#### Exposure

Patients will be considered unexposed to SUs until the time of the first SU prescription within ZODIAC. A one-year lag period will be accounted for. A lag period is necessary to take into account a latency time window and to minimise possible detection bias around the time of treatment initiation. Exposure to a SU will be classified according to one of the following, mutually exclusive, categories: gliclazide use, glimepiride use, tolbutamide use, glibenclamide use, non-SU use.

We aim to determine whether there are duration-response relationships between the use of SUs and obesity-related cancer incidence. Duration-response will be assessed in terms of cumulative duration of use, defined as the total number of years of use calculated by summing the durations of yearly prescriptions received between cohort entry and the time of the event and will be used as a time-dependent covariate.

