#### Patient selection

The study cohort entry date and baseline date will be the date the patients started participation in the ZODIAC cohort.

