#### Inclusion

All patients included will be participating in the ZODIAC-NCR cohort on or after January 1998 and will be users of SUs.

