#### Follow-up

All patients will be followed from the year of cohort entry until a diagnosis of cancer [3–5]. Patients with no diagnosis of cancer will be censored at the time of death, end of registration within the ZODIAC cohort or end of the study period (31 December 2012), whichever occurred first.

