#### Study endpoints

The primary outcome will be within-class SU difference in obesity-related cancer risk (see Table 1 for included cancers). The secondary outcomes will be all cancer risk (Table 2), site-specific cancer risk and the presence of a duration response relationship between SU use and cancer. Cancer sites of special interest will be specific cancers of the breast, colorectal, bladder, advanced prostate and lung cancer. Study endpoints will be evaluated for men and women separately.

**Table 1 Tab1:** Cancers included in primary endpoint obesity related cancer

Men	Women
Oesophageal (adenocarcinoma)	Oesophageal (adenocarcinoma)
Stomach cardia	Stomach cardia
Kidney	Kidney
Gallbladder	Gallbladder
Liver	Liver
Pancreatic	Pancreatic
Colorectal	Colorectal
Prostate cancer	Ovarian
	Breast
	Endometrial

**Table 2 Tab2:** Cancer excluded from secondary endpoint all cancer risk

Men (cancers excluded)	Women (cancers excluded)
Non-melanoma skin cancer	Non-melanoma skin cancer
Breast	Prostate
Ovarian	Male genital organs
Endometrial	
Female genital organs	

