#### Co-variates

Co-variates collected at cohort entry and annually thereafter are: age, sex, year of cohort entry, HbA1c (continuous), diabetes duration (time between diabetes diagnosis and cohort entry, continuous), BMI (continuous), serum creatinine (continuous), metformin use (yes, no), insulin use (yes/no), history of cancer (no non-melanoma skin cancer) (yes, no) and smoking (ever, never, unknown).

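### The class-wide SU duration-response slope rests on late starters and stoppers if the clock runs from ZODIAC entry, and event-free time before the first SU biases it upward

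*Protocol article*

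**What the plan says.** All references are to the Methods/design part of the protocol article.

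- **Time zero (Patient selection):** "The study cohort entry date and baseline date will be the date the patients started participation in the ZODIAC cohort".
- **Follow-up:** "All patients will be followed from the year of cohort entry until a diagnosis of cancer".
- **Population (Inclusion):** "All patients included will be participating in the ZODIAC-NCR cohort on or after January 1998 and will be users of SUs". Whether this means use at entry or at any time is not said. The Exposure section treats patients as unexposed until their first SU within ZODIAC, so some start after entry.
- **Outcome (Study endpoints):** a secondary outcome is "the presence of a duration response relationship between SU use and cancer".
- **Duration metric (Exposure):** "Duration-response will be assessed in terms of cumulative duration of use, defined as the total number of years of use", obtained by "summing the durations of yearly prescriptions received between cohort entry and the time of the event", and it "will be used as a time-dependent covariate". A one-year lag applies.
- **Exclusion:** patients with cancer diagnosed before they received an SU are left out. In the main analyses, patients who switch SU leave at the switch.
- **Covariates:** "Co-variates collected at cohort entry and annually thereafter are: age, sex, year of cohort entry", among others.
- **Primary analysis:** years on each specific SU enter the model and are updated annually.

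No section names the Cox time axis or gives the share of patients who start late or stop. The Abstract frames duration-response for individual SUs; Study endpoints and Exposure frame it for SU use in general.

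**The concern.** A Cox model compares patients who are at the same point on its time axis. A cohort of SU users, a follow-up clock that starts at ZODIAC entry and a duration count that starts at the same moment together mean that, for a patient who takes an SU throughout, years of use and time on the clock are the same quantity apart from the lag. Such patients cannot show whether risk rises with years of use.

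The contrast must then come from patients who start late or stop. For late starters the exclusion rule adds a second difficulty. Their time before the first SU has zero duration and, by construction, no events, because anyone with a cancer in that interval has been removed. Low duration is then paired with zero risk, which tilts the slope upward even when duration has no effect.

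Duration-response is a named secondary outcome, and the Background criticises earlier studies for not accounting for duration of use. A positive slope produced in this way could be reported as evidence of a cumulative drug effect.

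**Working it through.** The protocol article gives no sample size, event count or effect size for this outcome, so there is no figure to reproduce. The first two steps are algebra; the others use simulations with assumed inputs.

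**1. Class-wide duration on time since entry.** Let D(t) be lagged cumulative SU years at time t. For a patient on an SU from entry without a break, D(t) = t − 1 once t exceeds 1. The Cox information on a slope is the sum, over events, of Var(D | risk set). Among continuous users this variance is 0 at every t, and the lag does not help because it shifts them all equally. Example at t = 6: two continuous users each have 6 − 1 = 5 years; a patient who started at year 3 has 6 − 3 − 1 = 2 years. Only the late starter (or a stopper) differs.

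**2. Drug-specific durations.** With one term per SU, a continuous user has t − 1 years in one term and 0 in the others, so the four terms add up to t − 1 for everyone. Within these patients the information matrix has one zero eigenvalue, the slope common to all drugs. Each drug's own slope is not identified from them; differences between drug slopes are.

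**3. How much depends on the unknown mix.** Simulated cohort, clock from entry, annual updating, one-year lag, up to 10 years; assumed drug split 40/25/30/5% and event rate 1.5% per year.

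| Late starters / stopping per year | Correlation of D with clock | Share of D's variance usable within risk sets | Share of gliclazide-versus-other information from continuous users |
|---|---|---|---|
| almost none | 0.998 | 0.3% | 99.6% |
| 10% / 3% | 0.90 | 18% | 85% |
| 30% / 3% | 0.84 | 30% | 75% |
| 70% / 8% | 0.73 | 46% | 40% |

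**4. Event-free time before SU, true HR 1.00 per year.**

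- Entry clock, late starters 10 to 50%, 100 runs each: mean HR 1.055 to 1.060 with cancers before SU excluded, against 1.001 to 1.004 without that exclusion.
- 6,000 patients, 60% on an SU at entry and the rest starting over 8 years, 5% stopping per year, 40 runs: entry clock 1.070 with pre-SU time kept and 1.005 with delayed entry at first SU; attained age 1.062 and 1.001.
- A third set of runs, also on assumed inputs: entry clock 1.03 and 1.00; attained age 1.04 and 1.00.

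The bias follows the pre-SU time, not the time axis. Compounded over five years, 1.03 gives 1.03^5 = 1.16 and 1.07 gives 1.07^5 = 1.40.

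**5. What attained age buys.** Without further time covariates, the standard error of the log HR per year fell from 0.025 to 0.019 in one set of runs; in another it was 0.0145 on attained age against 0.0207 on the entry clock. With calendar year and year of entry both in the model it returned to 0.025 and 0.0207. The reason is arithmetic: calendar year minus entry year is time since entry. Attained age minus age at entry is also time since entry, and keeping baseline age on an age axis gave 0.0206. The gain therefore comes from assuming that time since entry has no effect of its own.

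**The case against.** The strongest objection is that the article never states the time axis, and that a condensed article may leave it to the full protocol or analysis plan. That stands: step 1 is conditional. Follow-up from entry with age listed as a covariate points to time since entry but does not settle it. The upward bias does not share this weakness, because it arises on both axes from the stated exclusion combined with counting time before SU.

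The second objection is that this is a within-class study, and the within-class question survives. That also stands. A reader might infer that the duration outcome cannot be estimated at all, or that the gliclazide comparison is undermined. The documents do not support either. Differences between drug slopes are estimable from continuous users, who carried between 40% and 99.6% of the information on gliclazide in the scenarios above. With many late starters the class-wide slope is estimable as well, though it then largely compares early with late starters.

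The third objection is that a change of time scale cures nothing by itself. That is correct. A reader might blame the spurious slope on the entry clock and expect attained age to remove it; step 4 shows that it does not. The precision gain is lost once year of entry, already on the covariate list, is kept beside calendar year.

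**Conclusion.** The point holds in a limited, conditional form.

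- **Conditional on time since ZODIAC entry as the axis:** the class-wide slope and each drug's own slope are identified only by late starters and stoppers. This is exact, not approximate. How fragile the slope is depends on their shares, which the document does not give; usable variance ran from 0.3% to 46% across the assumed mixes.
- **On either axis:** counting late starters' time before SU pushes the slope upward when there is no effect, by about HR 1.03 to 1.07 per year in the simulations. The direction follows from the exclusion rule; the size rests on assumed entry, stopping and event rates.
- **Not affected in this way:** differences between drug slopes on the first point, and hence the primary gliclazide comparison.

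The remedy needs no new data and serves a named secondary outcome, so it is worth making before the analysis.

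**What to change.** 1. In the duration-response models of the Exposure section, let each patient enter the risk set by delayed entry at the lagged first SU prescription, so that time before SU is not counted. Name the Cox time axis.
2. Make the within-class contrast the main duration result: the gliclazide-versus-other-SU hazard ratio in bands of years since first SU, or the difference between drug slopes.
3. If a class-wide slope is still reported, say that it rests on late starters and stoppers, and give their numbers.
4. Attained age may be shown as a sensitivity analysis. State that it gains precision only if calendar year and year of entry are not both adjusted for and baseline age is not kept, that is, by assuming no separate effect of time since entry. Disease progression after entry would then be read as duration of use, because diabetes duration is fixed at cohort entry.

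Cost: a change to the model statement, using dates already held. Person-time before the first SU is lost, and with it any class-wide statement against non-use. Events in the lag year also leave these models, much as they do in the third planned sensitivity analysis.

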An association between the class of SUs and increased overall cancer risk has also been reported [21–24]. Most previous studies are limited by methodological issues, for example many studies reported baseline SU use and did not account for duration of SU use [22–24]. There is also evidence suggesting within-class SU differences in cancer risk, where gliclazide use has been associated with a lower cancer risk [21–24]. There are several potential mechanistic explanations, one of which could be that gliclazide leads to a more selective glucose dependent insulin response and lower insulin levels. In what way and to what degree cancer risk is modified by different SUs in unclear and requires further investigation and confirmation.

Most evidence, however, is derived from small observational cohort studies and substantial knowledge gaps exist. This also holds true for the presumed favourable long-term cancer safety profile of gliclazide in particular. The relations between use of glucose lowering agents and cancer are complex and there is overlap in risk factors; for example, several glucose lowering agents have been associated with weight gain, which in itself has also been related to an increased cancer risk.

The primary aim of this study is to evaluate within-class SU differences in risk for obesity-related cancer (excluding non-melanoma skin cancers) accounting for weight changes during follow-up and drug exposure [6]. Secondary aims are to evaluate within-class SU differences concerning all cancers combined and the cancer risks of the five largest groups of site specific cancers (breast, colorectal, prostate, bladder and lung cancer) accounting for duration of drug use.

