### Study population

#### Combined ZODIAC-NCR cohort

All cancer events that occurred between 1 January 1989 and 2012 were linked to the data of the ZODIAC study via a trusted third party using postal code, full name, date of birth and sex. The medical ethics committee of Isala, Zwolle, the Netherlands approved the linkage of ZODIAC and NCR (METC reference number 13.0765). The NCR expected that the number of false-positive and the number false-negative linkage is both under 1%. By combining the two databases a cohort composed of patients diagnosed with T2D between 1 January 1998 and 31 December 2012 was assembled.

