#### Exclusion

Patients treated with long-acting or mixed insulin before oral glucose lowering agents and those receiving insulin on top of SU at study entry will be excluded. Patients who received a cancer diagnosis before receiving a SU will be excluded. For the main analyses patients who switch medication within the class of SUs will be excluded at the time the switch occurs.

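### Cumulative SU years are counted only from ZODIAC entry while patients already on an SU stay eligible, so their earlier use scores zero in the primary exposure term

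*Protocol article*

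**What the plan says.** All sections are in the Protocol article.

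- **Patient selection** sets time zero: "The study cohort entry date and baseline date will be the date the patients started participation in the ZODIAC cohort".
- **Inclusion** asks that patients take part "on or after January 1998 and will be users of SUs". It does not require an SU-free period first.
- **Exclusion** foresees SU use at entry, because "those receiving insulin on top of SU at study entry will be excluded". SU use at entry without insulin is not an exclusion.
- **Exposure** starts the clock inside the cohort: "Patients will be considered unexposed to SUs until the time of the first SU prescription within ZODIAC". Duration is then obtained by "summing the durations of yearly prescriptions received between cohort entry and the time of the event". A one-year lag applies.
- **Co-variates** includes "diabetes duration (time between diabetes diagnosis and cohort entry, continuous"), so diabetes may precede entry.
- **Primary analysis** enters SU exposure as cumulative years on a specific SU and adjusts for the baseline covariates.
- **Sensitivity analysis** lists six analyses. None restricts to new users or recovers SU years before entry.

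**The concern.** Duration is central to this plan. It is the exposure in the primary model, and the Background faults earlier work because "many studies reported baseline SU use and did not account for duration of SU use". Yet for anyone who arrives already on an SU, the count restarts at zero on the day of entry. A patient with several years of prior use and a true starter get the same score after the same time in the cohort.

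Two things are at stake. The first is the duration-response estimate, since part of the true exposure of these patients is absent from the variable meant to measure it. The second is the within-class comparison. If users of one SU tend to bring more uncounted years than users of another, any effect of those years can appear as a difference between drugs.

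**Working it through.** **1. Reading the rules together.** Take a patient on an SU, without insulin, when ZODIAC participation begins.

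| Plan element | What happens to this patient |
|---|---|
| Inclusion and Exclusion | Stays in |
| Cumulative duration | Pre-entry SU years score zero |
| One-year lag | Runs from the first recorded prescription, not the true start |
| Sensitivity analysis 2 (confounders from the year before first SU) | No ZODIAC record exists for that year |
| Sensitivity analysis 3 (drop events in the year after SU start) | Drops the year after entry, not the year after the true start |

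**2. Inputs for size.** The article gives no sample size, event count, share of prevalent users or prior SU years, so there is no stated figure to reproduce. Every input below is an assumption.

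**3. Share of true duration lost.** With p prior years and f counted years, the share scored as zero is p / (p + f).

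| f | p = 1 | p = 2 | p = 5 | p = 10 |
|---|---|---|---|---|
| 3 | 25% | 40% | 62% | 77% |
| 5 | 17% | 29% | 50% | 67% |
| 8 | 11% | 20% | 38% | 56% |

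**4. Effect on the per-year slope.** Simulation assumptions: true HR 1.05 per SU-year for both drug groups, base hazard 0.02 per year, 8 years of follow-up, new users starting in years 0 to 4, exponential prior use in prevalent users, 8 runs of 20,000 patients, Poisson model with yearly strata, no adjustment for diabetes duration.

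| Prevalent share | Mean prior years, gliclazide / other | Fitted HR per scored year, gliclazide / other |
|---|---|---|
| 30% | 3 / 3 | 1.09 / 1.09 |
| 60% | 3 / 3 | 1.10 / 1.10 |
| 30% | 2 / 6 | 1.09 / 1.11 |
| 60% | 2 / 6 | 1.11 / 1.14 |

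When the pre-entry years are counted, all four rows return about 1.05. With equal prior use the slope is wrong but the between-drug ratio is about 1.00. With unequal prior use a false ratio (other to gliclazide) of about 1.02 to 1.03 per year appears. The slope rises here because prevalent users have both more scored years and uncounted risk. That direction belongs to the assumed set-up and is not a general result.

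**5. Effect on a gliclazide-versus-other contrast, and the planned adjustment.** Assume identical drugs (HR 1.04 per true year), half of patients prevalent, and mean prior use of 2 years for gliclazide against 5 for the others.

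- Hand check using the means: 0.5 × (5 − 2) × ln(1.04) = 0.5 × 3 × 0.0392 = 0.059, and exp(−0.059) = 0.94, where the truth is 1.00.
- Simulated without adjustment: about 0.92 to 0.95.
- With diabetes duration at entry added: about 0.96 to 0.99.
- The result depends on the gap between diabetes diagnosis and SU start. In 40 cohorts of 9,000 (Monte Carlo SE about 0.01 on the log scale), the adjusted value was 1.005 with a mean gap of 1 year and 0.98 with 3 years. With 5 years it moved only from 0.91 to 0.93.
- On the per-year scale that the primary model uses, the gliclazide-to-other ratio was about 0.98 unadjusted and 0.986 to 0.995 adjusted.
- New users only: about 1.00 to 1.01.
- All users with a prevalent-use indicator but no diabetes duration: still 0.92 to 0.95. The indicator does not know how long each patient had been treated.

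**The case against.** The strongest reply is that the primary model already adjusts for diabetes duration at entry, age and year of entry. SU years before entry lie inside diabetes years before entry, so diabetes duration is a reasonable proxy. This stands in part: where SU treatment follows diagnosis closely, adjustment removes most of the contrast bias. Where the gap is long and variable, it removes little. It is not a measure of SU duration.

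Second, prior use may be short. The Combined ZODIAC-NCR cohort section describes a cohort of "patients diagnosed with T2D between 1 January 1998 and 31 December 2012 was assembled". Read literally, this caps pre-entry use at the entry year minus 1998, for example 10 years for entry in 2008. The Background also places SUs as a second step after metformin. Both limit the problem, and neither removes it.

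Third, if patients without a pre-SU record drop out of sensitivity analysis 2, that analysis approximates a new-user subset. The plan does not say they are dropped, so this is at best an accidental remedy. The planned zero-lag repeat likewise eases the lag point but restores no earlier years.

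Fourth, the Data source sections list medication use but no SU start date, so earlier years may be unrecoverable. That is fair, and it argues for restriction rather than reconstruction.

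A reader might go further and infer that the gliclazide comparison is biased by a known amount, such as an HR of 0.94. The article does not support this. That value is unadjusted, is not on the cumulative-years scale of the primary model, and rests on a difference in prior use that appears nowhere in the article.

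**Conclusion.** The concern holds as a defect in a stated rule, not as missing detail. The eligibility rules keep patients already on an SU, and the Exposure section discards their earlier years from the primary exposure term and mis-dates their SU start. No planned analysis is specified to correct this.

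For the duration-response aim, exposure is mismeasured for every such patient, whether or not prior use differs between SUs. For the within-class contrast, bias needs prior use to differ between SUs, which the article neither shows nor rules out. The planned adjustment then leaves a remainder that depends on the unknown gap between diagnosis and SU start.

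The size cannot be fixed from the article. Under the assumptions shown, the remaining contrast bias ranges from negligible (1.005) to about 7% (0.93). This should be addressed before analysis, but it does not by itself invalidate the study.

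**What to change.** Prespecify a new-user analysis: patients with at least one SU-free annual ZODIAC record before their first SU prescription. Make it the primary analysis if the event count allows. Otherwise make it a key sensitivity analysis reported beside the all-user analysis. In either case, base the duration-response conclusion on new users, for whom scored and true duration agree as far as the records show. The same restriction dates the lag from a recorded SU start and makes sensitivity analyses 2 and 3 workable.

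If the all-user analysis is kept, report how many patients were on an SU at entry, by drug. Do not rely on a prevalent-use indicator alone, since it left the contrast bias in place in the check above.

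The work is one eligibility definition and a filter on annual records already held. The price is fewer patients and events and wider intervals in that analysis. If half of users were prevalent at entry, at least half of the cohort would leave it, so the event count should be looked at, without reference to drug, before its status is fixed.
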